### Sample size determination

For sample size calculation, we set up a simulation study and used multiple regression to predict the change in OSS within 6 months for the most important prognostic factors. The prognostic factors were derived from an existing ARCR local registry^66^ and include age, sex, body mass index/obesity status, tendon quality/degeneration and rotator cuff severity.^31–35^ We accounted for type I error at 5% for statistical significance and type II error set at 20% for 80% statistical power.^67^ Two thousand replications were done, and the p values were recorded to calculate the mean significance for each of the prognostic factors to reach a minimum of 80% statistical power. This approach led to a sample of 920 patients.

For the second primary outcome of shoulder stiffness, we accounted for a minimum of 10 events per variable to allow for the inclusion of a maximum of 10 predictors into the model.^68 69^ The estimated event rate for shoulder stiffness from our pilot data set was 8.3%, which according to our experience might reflect an underestimation of the true rate.^17^ Therefore, a 10% stiffness rate was assumed, which resulted in a sample size calculation of 900 patients.

The higher resulting number determines the final number of patients to be recruited. Therefore, 920 patients will be included with an additional 50 patients (ie, 970 patients) due to the anticipated maximum dropout rate of 5% at 6 months (based on personal experience).

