### Baseline prognostic factors

Various baseline parameters, operative details and postoperative management variables are known or suspected to influence ARCR outcomes.^31–35^

The following patient-related factors will be recorded: patient demographics (year of birth, age, sex), socioeconomic parameters (nationality, marital status, highest level of education, employment status, last occupational position, daily physical workload), dominant side, smoking and drinking status, general physical and mental health (body mass index and obesity), American Society of Anesthesiologists classification, comorbidities (eg, diabetes), concomitant medication, level of depression and anxiety (PROMIS Depression and Anxiety Short Form 4a),^47 48^ and quality of life (EQ-5D-5L).^53^

Disease-related factors are shoulder clinical examinations (pain level on NRS, range of motion, muscle strength, CS^44^), patient-reported shoulder function (see Outcomes section), radiograph parameters (critical shoulder angle,^54^ acromiohumeral distance^55^), MRI or arthro-CT parameters (supraspinatus muscle atrophy,^56^ tangent sign,^57^ grade of fatty infiltration^58 59^) and medical history (cause of injury (trauma event), symptom duration, previous interventions (operation and timing of surgery), actual medication, extent of physical therapy).

Rotator cuff integrity and concomitant local findings will be investigated. The rotator cuff tear will be determined by MRI (or arthro-CT) and confirmed intraoperatively: tear size, location (involved tendons) and grading (partial/complete), tendon retraction grade^60^ and tear sagittal size,^61^ status of the biceps tendon, and additional intraoperative observation of concomitant local injuries (superior labrum from anterior to posterior (SLAP) lesion, humeral avulsion glenohumeral ligament, Bankart lesion, humeral and glenoid-side chondral lesions).

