### Predictive model development

To develop the predictive model(s), the seven steps proposed by Steyerberg *et al*^72 73^ will be used. The steps comprise (1) consideration of the research question and initial data inspection; (2) coding of the predictors; (3) model specification; (4) model estimation; (5) evaluation of model performance; (6) internal validation; and (7) model presentation.

Depending on the type of outcome, different models will be fitted and evaluated, that is, multiple regression models for the change in OSS at 6 months and multivariable logistic regression models for shoulder stiffness. Model diagnostics will be performed for all models to check the underlying assumptions.

The prediction of the model(s) will be based on the baseline, operative and postoperative management variables. First, a subset of the potential prognostic factors will be defined based on whether it is thought to be most predictive. The subset will be selected separately for each outcome by the Delphi method among the investigators, whereby the factors will be noted for their known or potential prognostic value on a 5-point Likert scale from 1 (not important) to 5 (extremely important). The factors with the highest mean score among investigators will form the subset.

We will then use criterion-based procedures (eg, Akaike information criterion or adjusted R^2^) to select the best set of predictors for the continuous outcome(s), and for the binary outcome we will use the area under the receiving operating characteristics curve.

To assess the predictive performance of the final models as well as the updated version of the prediction models, calibration plot and discrimination measures will be used. Thereby, apparent performance will be evaluated on the respective development data, and internal validated performance will be determined by bootstrapping. Independent external validation will be estimated by applying the resulting models from the development data set in the respective validation data sets. The resulting models will be used to predict the change of outcome value (ie, OSS in 6 months) and assess whether a patient will experience the event (ie, shoulder stiffness).

If we observe missing data, then missing data imputation will be performed using a method that allows for uncertainty in the imputed values (eg, multiple imputations using chained equation^74^). We will account for the clustering of records within clinics as appropriate.

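### The stiffness event budget counts predictors kept in the model, not the candidate parameters screened against the outcome, so the plan's minimum of 10 events per variable is not secured

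*Protocol article*

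**What the plan says.** The article's section on sample size determination justifies the number of patients for the second primary outcome by an events-per-variable rule: "we accounted for a minimum of 10 events per variable to allow for the inclusion of a maximum of 10 predictors into the model". It then fixes the rate and the result: "Therefore, a 10% stiffness rate was assumed, which resulted in a sample size calculation of 900 patients". The pilot figure behind that rate was lower: "The estimated event rate for shoulder stiffness from our pilot data set was 8.3" per cent, which the authors think may be too low. The final number comes from the other primary outcome, change in the Oxford Shoulder Score: "Therefore, 920 patients will be included with an additional 50 patients (ie, 970 patients"), allowing for an "anticipated maximum dropout rate of 5% at 6 months".

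The section on predictive model development describes how predictors reach the stiffness model. Investigators first rate the potential factors in a Delphi exercise, separately for each outcome: "The factors with the highest mean score among investigators will form the subset". The data then choose among these: "for the binary outcome we will use the area under the receiving operating characteristics curve". The text gives neither a subset size nor a score cut-off, and does not refer back to the 10 predictors. Internal validation is by bootstrap; the text does not say whether selection is repeated within each sample.

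The section on baseline prognostic factors lists several dozen items. Many are graded or have several categories, for example "tear size, location (involved tendons) and grading (partial/complete), tendon retraction grade", fatty infiltration grade, ASA class, education and employment status.

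**The concern.** An events-per-variable rule is meant to limit overfitting. When the outcome data decide which predictors stay, every parameter compared with the outcome uses up information, whether or not it survives. The right denominator is the number of candidate parameters entering the data-driven step. The sample size section instead counts what is finally included, and counts each predictor as one even if it needs several coefficients.

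A model that keeps 10 predictors would meet the rule as worded whether the selection began with 10 candidates or with 30. The more candidates are screened, the more the fitted risks tend to be too extreme and the more the apparent discrimination flatters the model. Stiffness is one of two primary outcomes, and the article wants the models to give individual risks that support the decision for surgery, so calibration matters here.

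**Working it through.** **Inputs, all from the sample size section:** 10 events per variable; at most 10 predictors; stiffness rate 10% (assumed) or 8.3% (pilot); 920 evaluable and 970 recruited patients; 5% dropout. The number of candidate parameters is not stated, so 10 is used as the reference and 15, 20 and 30 are shown as assumptions.

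**Step 1: the plan's own figures.** Patients needed = events per variable × predictors / rate.
- At 10%: 10 × 10 / 0.10 = 1000, not the stated 900. The 900 would follow from 9 predictors (9 × 10 / 0.10) or from a rate of 100 / 900 = 11.1%.
- At 8.3%: 100 / 0.083 = 1205.
- Dropout: 920 / 0.95 = 969 after rounding up, in line with the stated 970.

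The gap between 900 and 1000 is a separate error. The unit problem would remain if 100 events were observed.

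**Step 2: expected events among 920 evaluable patients.**
- At 10%: 920 × 0.10 = 92.0
- At 8.3%: 920 × 0.083 = 76.4

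**Step 3: events per candidate parameter** = expected events / candidate parameters.

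| Candidate parameters | 10% rate | 8.3% rate |
|---|---|---|
| 10 | 9.2 | 7.6 |
| 15 (assumed) | 6.1 | 5.1 |
| 20 (assumed) | 4.6 | 3.8 |
| 30 (assumed) | 3.1 | 2.5 |

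With no dropout at all, 970 × 0.10 = 97 events give 9.7 for 10 parameters. Ten parameters reach 10 events each in 920 patients only if the rate is at least 100 / 920 = 10.9%.

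**Step 4: the largest candidate set that keeps the minimum at 920 patients.** 92.0 / 10 gives 9 parameters at 10%; 76.4 / 10 gives 7 at 8.3%.

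**Step 5: illustration of the consequence, under assumptions.** Logistic simulation with 921 patients and about 90 events; independent standard normal candidates, five of them with a log-odds ratio of 0.32 and the rest noise; backward elimination by Wald statistic to 10 predictors; 300 replicates; validation in 20,000 patients.

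| Candidates | External calibration slope | External AUC | Apparent AUC |
|---|---|---|---|
| 10 | 0.79 | 0.67 | 0.71 |
| 20 | 0.68 | 0.66 | 0.72 |
| 30 | 0.60 | 0.65 | 0.73 |
| 40 | 0.56 | 0.65 | 0.74 |

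A second run with 200 replicates gave nearly the same slopes (0.78, 0.68, 0.61 and 0.56). All four models keep 10 predictors, so the rule as worded does not distinguish them. Effect sizes, independence, pure-noise extra candidates and Wald elimination are assumptions; the plan selects by AUC.

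**The case against.** A reader might infer that the Delphi subset is larger than 10 and that the effective ratio is well below 10. The article does not support this as fact. It never gives the subset size. A subset of 10 one-parameter factors, from which fewer are kept, fits the text and gives 9.2 events each at 10%. The ratios for 15 or more parameters, and the simulated slopes, depend on assumed counts.

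Nor are the several dozen listed factors all tested against stiffness. The Delphi step reduces them by investigator rating without using outcome data, so it spends no events. Coding of predictors is also a named step of the development process, and graded factors could be entered there as single terms; nothing says that they will be sets of indicators. Subset size and coding may well be settled in an analysis plan that is not shown.

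Bootstrapping also answers part of the harm. In a small check (40 replicates, 20 bootstrap samples each, so approximate) with 30 candidates and selection repeated in every sample, an apparent AUC of 0.72 was corrected to 0.65, equal to the true value. The fall in true AUC is small, from 0.67 with 10 candidates to 0.65 with 30. Reducing 10 candidates to 6 gave a slope of 0.83, so selection as such need not hurt.

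These points limit the size of the claim but do not remove it. Corrected performance figures report overfitting honestly; they do not undo the extra overfitting in the coefficients. And the sample size rationale is given in this article, in a unit that does not match the selection procedure given in the same article.

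**Conclusion.** The point holds as a mismatch between two sections. The minimum of 10 events per variable is set for retained predictors, while the analysis selects by AUC from a subset not linked to that number and from factors that may need several parameters. The minimum is therefore not secured for the parameters examined against stiffness.

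On the plan's own figures it is missed whenever the full 10 are used: 9.2 events per parameter at 10% and 7.6 at 8.3%. It is met with 9 or fewer candidate parameters at 10%, or 7 or fewer at 8.3%. A ratio of about 6 or lower at the 10% rate requires 15 or more candidate parameters, which is possible under the text but not stated. The change is worth making because it affects a primary model and needs wording only.

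**What to change.** 1. **Sample size determination:** state the budget as candidate parameters (regression degrees of freedom, counting every category and non-linear term) examined against stiffness, in place of predictors included in the model. Correct the 900 at the same time.
2. **Predictive model development:** before any association between a predictor and stiffness is examined, cap the stiffness Delphi subset at the top-ranked factors whose parameters together do not exceed the total number of events divided by 10. That is about 9 parameters at 10% and 7 at 8.3%. Only the expected or the overall observed event count is used, so the cap stays blind to predictor effects. Enter ordinal grades as linear or two-level terms where needed to stay within it.
3. **Internal validation:** state that the whole selection step is repeated in each bootstrap sample.

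The cost is a change of wording, with no extra patients or data. Fewer factors can be considered for stiffness; lower-ranked ones move to an analysis labelled exploratory, and single-term coding of grades may lose some detail. The cap limits overfitting but does not abolish it: under the simulation's assumptions, 9 candidates still gave a calibration slope of about 0.81.

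### The stiffness sample size of 900 does not follow from its stated inputs, which give 1000, so the planned cohort falls slightly short of its own events-per-variable rule

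*Protocol article*

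**What the plan says.** The section on sample size determination in the protocol article makes one calculation for each primary outcome.

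- **OSS change at 6 months.** A simulation of multiple regression at 80% power is reported, with the result: "This approach led to a sample of 920 patients".
- **Shoulder stiffness within 6 months.** The criterion is "a minimum of 10 events per variable to allow for the inclusion of a maximum of 10 predictors into the model". The rate is then fixed in two steps. First comes the pilot figure: "The estimated event rate for shoulder stiffness from our pilot data set was 8.3" per cent, which the authors think may be too low. Then: "Therefore, a 10% stiffness rate was assumed, which resulted in a sample size calculation of 900 patients".

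The two results are combined by a stated rule: "The higher resulting number determines the final number of patients to be recruited". With 920 for the OSS and 900 for stiffness, the OSS governs, and the target follows: "920 patients will be included with an additional 50 patients (ie, 970 patients) due to the anticipated maximum dropout rate of 5% at 6 months".

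The section on predictive model development confirms that stiffness will be modelled by multivariable logistic regression. Neither section gives any further input to the 900.

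**The concern.** The three inputs for stiffness (10 events per variable, 10 predictors, a 10% rate) fix the answer, and it is not 900. The figure also feeds a decision, because the cohort size is the larger of two numbers. An understated stiffness figure can change which primary outcome drives recruitment.

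What is at stake is a stated design property of a primary model. A reader of the article will take it that the cohort provides at least 10 events for each of up to 10 predictors of stiffness at the assumed rate. If it does not, either the recruitment target or the permitted number of predictors is misstated.

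**Working it through.** **Inputs, all from Sample size determination**

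- Events per variable (EPV): 10, as a minimum
- Predictors: 10, as a maximum
- Stiffness rate: 10% assumed, 8.3% in the pilot data
- OSS sample size: 920
- Dropout at 6 months: at most 5%; planned cohort 970

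**Step 1. Try to reproduce 900.** The formula is N = EPV x predictors / rate.

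- Stated inputs: 10 x 10 / 0.10 = 1000. The figure of 900 is not reproduced.
- Pilot rate: 10 x 10 / 0.083 = 1205.
- Intercept counted as an eleventh parameter: 10 x 11 / 0.10 = 1100.
- Dropout applied to 1000: 1000 / 0.95 = 1053 upwards, or 1000 x 0.95 = 950 downwards.

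None of these gives 900. It appears only if a stated input is changed:

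- 9 predictors: 10 x 9 / 0.10 = 900
- 9 events per variable: 9 x 10 / 0.10 = 900
- a rate of about 11.1%: 100 / 0.111 = 901

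The text does not show which of these, if any, lies behind the figure.

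**Step 2. Carry 1000 through the protocol's own rule.**

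- As written: max(920, 900) = 920, and 920 / 0.95 = 968.4, which agrees with the planned 970.
- Corrected: max(920, 1000) = 1000, and 1000 / 0.95 = 1052.6, so about 1053 to recruit. That is 83 more than 970.

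**Step 3. What the planned cohort delivers.** Expected events = N x rate. EPV is for 10 predictors, and the last column is events / 10 rounded down.

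| Patients with outcome | Rate | Expected events | EPV | Predictors at 10 EPV |
|---|---|---|---|---|
| 900 | 10% | 90 | 9.0 | 9 |
| 920 | 10% | 92 | 9.2 | 9 |
| 970 (no dropout) | 10% | 97 | 9.7 | 9 |
| 920 | 8.3% | 76.4 | 7.6 | 7 |
| 970 (no dropout) | 8.3% | 80.5 | 8.1 | 8 |

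**Step 4. How far off is 100 events?**

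- Rate needed: 100 / 920 = 10.9% with 920 patients; 100 / 970 = 10.3% with 970.
- If the true rate is 10% and the event count is binomial, the chance of at least 100 events is about 20% with 920 patients and 39% with 970.

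**The case against.** The arithmetic is hard to dispute; the case on the other side concerns its consequences.

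- **Ten is a ceiling.** A 9-predictor model meets the rule with 920 patients (92 / 9 = 10.2 events per variable). This stands as a limit on the consequence. It does not rescue 900, because the calculation is said to allow for 10.
- **The 10% rate is disclosed and reasoned.** The authors report 8.3%, say why they think it low, and cite support. Stiffness will also be identified from clinical records and from clinician and patient reports, as well as by the consensus definition (Outcomes), which may find more cases. This stands: the 8.3% results are a sensitivity case and not an error in the plan.
- **Little harm to the model.** A reader might infer that the cohort cannot support a 10-predictor model, or that its predictions will be seriously over-fitted because of this slip. The documents do not support that. As an illustration, assume a model R2 of 15% of its maximum (0.15 x 0.478 at a 10% rate; the 15% is an assumption) and solve n = p / ((S - 1) ln(1 - R2/S)) for the shrinkage factor S. With p = 10 parameters, S is 0.873 at n = 920 and 0.882 at n = 1000, a difference of about 0.01. With 20 parameters the values are 0.776 and 0.790, and with 30 they are 0.699 and 0.716. Over-fitting depends far more on the number of parameters than on 920 versus 1000. The protocol also plans bootstrap internal validation and calibration plots, which would expose optimism.
- **Candidate predictors.** One might go further and count events against every candidate screened. The article plans an outcome-specific Delphi shortlist before data-driven selection but gives no size for it, so any particular number of candidates would be a guess. That detail can properly sit in the full protocol or analysis plan.

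**Conclusion.** The point holds as an error in a stated figure with a modest consequence. From the protocol's own inputs the stiffness sample size is 1000, not 900. Under its own rule stiffness, not the OSS, would have set the cohort size, at about 1053 to recruit instead of 970.

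The planned cohort misses its own criterion by a small margin: 9.2 events per variable in expectation with 920 evaluable patients, and 9.7 even if nobody drops out. It supports 9 predictors where the plan says up to 10. If the pilot rate held, it would support about 7.

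This rests on the stated rate, the stated EPV rule and one parameter per predictor. It should not be read as saying that the stiffness model is infeasible, that 10% is the wrong assumption, or that 970 patients are too few for a useful model. Nor can the source of 900 be identified: 11.1% is the top of the literature range in the Introduction, but 9 predictors or 9 events per variable explain the figure equally well.

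**What to change.** Keep the 970 patients and correct the text of the sample size section, and of the analysis plan if it repeats the figure:

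- Replace 900 by 1000 as the result for 10 events per variable, 10 predictors and a 10% rate.
- State that the cohort stays at 970, and that 920 evaluable patients are expected to give about 92 events. These support at most 9 predictor parameters in the stiffness model at 10%, or about 7 if the pilot 8.3% holds.
- Amend the sentence on the higher number, since 920 is no longer the higher of the two.

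Alternatively, if 900 came from an input that the text does not report, state that input and make the sentence agree with it.

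Raising the target to about 1053 would also restore consistency, but the small shortfall does not require it. The recommended change costs only wording and a slightly less favourable stated number of predictors, with no extra patients.

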### Recruitment

Study sites and local investigators were selected based on their expertise in ARCR, with support from the shoulder and elbow expert group of Swiss Orthopaedics. Each site was visited by the project leaders to assess the adequacy of local clinical and research settings for the project as well as to ensure prior interest and commitment. The number of included sites was determined based on the reported estimate of the number of ARCR patients that could be realistically enrolled within 1 year from each site and included an allowance for overestimation (ie, all sites together estimated that they could recruit up to 40% more than the expected 970 patients within 1 year).

Patients who are enrolled after signing an informed consent form are definitively recruited for the project after documentation of baseline parameters (clinical examinations and patient questionnaires) and confirmation of ARCR during surgery. A recruitment curve is prepared every 2 weeks and sent to the project sites along with a recruitment table presenting the performance of each site. Sites that are unable to recruit the expected number of patients within the first 3 months will be considered for exclusion from the project and replaced by additional sites if the estimated total duration of patient enrolment is delayed for more than 3 months.

### Data collection methods

Data are collected on electronic or paper-based case report forms or patient questionnaires. Project parameters and used instruments are presented in the previous sections of this protocol. A training video was prepared for the collection of CS data.^44^ For the measurement of shoulder muscle strength, several devices were permitted, that is, IsoForceControl (MDS Medical Device Solution, Oberburg, Switzerland), Mark-10 Force Gauge (Mark-10 Corporation, Copiague, USA), as well as hand-held (Lafayette Instrument, Lafayette, USA) or MicroFET 2 (Hoggan Scientific, Salt Lake City, USA) dynamometers; the use of a spring balance was not allowed.

Patient clinical examinations, including baseline imaging assessments, are performed at each site by experienced clinicians (who may be assisted by locally trained research staff) and documented primarily on paper-based case report forms. Baseline MRI and radiographs are coded and centralised at the University of Basel to ensure data quality control. Operative data are collected electronically by the respective surgeons shortly after surgery. Patients complete the questionnaires in their preferred language, which is limited to German, French, Italian or English, either electronically after invitation, by email or on a tablet computer at the site, or otherwise on paper. AEs are documented electronically by the respective surgeons with support from their research staff. Data collected on paper forms are entered electronically at each site or at a central location at the University of Basel based on the agreement made with each site.

